### Outcome Measures

#### Primary Outcome Measure

##### Flow-Mediated Dilation

FMD is a non-invasive technique and the gold standard to measure endothelial function. The FMD measurement will be performed at the brachial artery, at the non-dominant side, following a standardized protocol described by Thijssen et al. (67). An ultrasound system (GE, Vivid 7) with a linear probe (12L, 7–10 MHz) will be used to assess the brachial artery diameter based upon longitudinal images with the lumen–intima interface visualized on both (anterior and posterior) walls. The arterial occlusion will be performed *via* a sphygmomanometer cuff (Hokanson, SC5™, 6 × 83 cm), placed 5–10 cm below the elbow, inflated and held between 220 and 240 mmHg (68, 69) for 5 min. For stability, the probe will be hold tight by a stand-off probe support. To assess the effect of the reactive hyperemia, the brachial artery will be visualized pre-occlusion for 90 s (mean of three individual clips comprising each 30 s) and post-occlusion for 4 min with additional 15 s before cuff release. Although it is recommended to perform an FMD measurement in fasting state (67), this is not feasible since the entire protocol lasts around 5 h. However, the measurements will be done 15 and 150 min after food intake (standardized breakfast at each visit). Boundaries for diameter measurement will be identified automatically by means of a boundary tracking software (Quipu, diastolic phase) and optically controlled by a single, independent and blinded investigator. When tracking is impaired, the investigator will restore this tracking with maintenance of region of interest. Data obtained from false tracking or altered region of interest will be removed from analysis. FMD measurement is a challenging technique and has a significant learning curve. At least 100 scans supervised by a specialist were done prior to the start of this study.

#### Secondary Outcome Measure

##### Blood Pressure

BP measurements will be carried out at the dominant side, in sitting position, after 3 min of rest by an automatic device (Tango+, SunTech Medical). Heart rate and systolic and diastolic BP will be assessed for 21 min with an interval of 3 min, pre- and post-capsules intake. During the recording, participants will be asked to remain calm and silent and refrain from drinking. Systolic and diastolic BP, as well as mean arterial pressure, pulse pressure, and heart rate will be used in analysis.

##### Dynamic Handgrip Exercise Test With Near-Infrared-Spectroscopy

A maximal dHGE will be performed with simultaneous NIRS (OxiplexTS, ISS, Champaign, IL, USA) monitoring to assess the oxygenation and vasoreactivity at the level of arterioles and capillaries of Musculus flexor digitorum superficialis, Musculus flexor carpi ulnaris, and Musculus flexor carpi radialis. A reliable handgrip exercise protocol, specifically designed for patient populations using NIRS measurements, will be carried out according to Celie et al. (70). In order to minimize bias and to work with relative values, an arterial occlusion of the ipsilateral upper arm will be performed by a pneumatic cuff (Hokanson, SC5™, 6 × 83 cm) inflated and held between 220 and 240 mmHg for 5 to maximal 7 min, until maximal deoxygenation (hemoglobin and myoglobin) values are reached (71). In this study, the maximal voluntary contraction will be calculated by means of two attempts with 10 s in between. The exercise test, consisting of 2-min periods of an incremental cyclic contractions protocol (1 s contraction, 1 s relaxation) followed by 1-min rest periods, will start at 20% of the maximal voluntary contraction and increase by 10% of the maximal voluntary contraction each step until exhaustion. Total hemoglobin [sum of deoxy- and oxyhemogblin, which reflects the change in regional blood volume (72)], deoxyhemoglobin and –myoglobin, and saturation will be assessed according to Celie et al. (70).

Blood flow through the brachial artery *via* echo-doppler will be measured according to Celie et al. (71) (same transducer and linear probe as used for the FMD measurement) at baseline (before cuff occlusion), immediately after cuff occlusion, and in the periods of rest after each increasing step.

##### Blood Analyses

Levels of uric acid (photometry, Architect c16000, Abbott), vitamin C (colorimetric method, R-biopharm/Roche reagent, Indiko Plus, Thermo Fisher), and glucose (photometry, Architect c16000, Abbott) will be measured at each study day in whole blood (anticoagulant-free tubes). Plasma and serum derived from EDTA and anticoagulant-free tubes will be centrifuged (3,500 g for 10 min at 10°C) and thereafter stored at −80°C together with a cryovial whole blood in the medical biobank of the Ghent University Hospital (Bioresource center Ghent, Gent, Belgium, ID: BE 71067049) (73). At the end of the study, cholesterol (photometry, Architect c16000, Abbott), high density lipoproteins (photometry, Architect c1600, Abbott), triglycerides (photometry, Architect c16000, Abbott), high sensitive C-reactive protein (particle-enhanced immunonephelometry, BN II, Siemens), vitamin E (liquid/liquid extraction followed by detection *via* UPLC-DAD), free fatty acids (enzymatic colorimetry, Cobas 8000 e801, Roche Diagnostics), and free insulin (Cobas e801 Roche, ECLIA) will be determined in serum, while hemoglobin A1c (exchange chromatography—Tosoh HLV-723 G8) and haptoglobin (Behring Nephelometer analyzer II), a marker of iron metabolism (74), will be determined in whole blood. All samples will be analyzed at the lab of clinical biology of Ghent University Hospital.

#### Additional Outcome Measures

In each participant, physical activity [steps per day and moderate-to-vigorous physical activity (MVPA)] will be evaluated with an accelerometer [Actigraph wGT3X-BT, dominant side, hip (75)] and glycemic excursions (percentages of time in hyper- or hypoglycemic ranges and time in range), risk for hypo- and hyperglycemia (Low and High Blood Glucose Indexes, LBGI and HBGI), and glycemic variability [standard deviation, coefficient of variation, and mean amplitude of glucose excursion (MAGE)] (76) by continuous interstitial glucose measurement (blind mode, IPro2, Medtronic, abdomen) for 1 week, immediately after the second study day. During this week, the above-mentioned restrictions concerning food intake and physical activity are not applicable and participants are encouraged to maintain their normal daily habits. Additionally, participants are asked to fill in a diary concerning their food intake and their physical activities for each day.

### Statistical Analyses

#### Power and Sample Size Calculation

Sample size calculations are based on previous research focusing on interventional studies with FMD measurements (77, 78) who established that in cross-over trials at least 20–30 participants are required for a minimal detectable change of 1.5–2% in FMD (80% power, alpha-level = 0.05). Sample size calculation was done by SAS power and sample size, indicating a minimum of nine participants in each group (41). Data will be analyzed taking into account volunteer- and methodology-related factors (79).

#### Data-Analysis Plan

Effects of CF ingestion on primary and secondary outcome measures will be evaluated within and between groups. Data will be analyzed using a random intercept model in mixed models. Fixed effects will be the group, the supplementation (cocoa flavanols vs. placebo), the time (pre- vs. post-intake of capsules) during each visit for repeated measurements, as well as group × supplementation interaction and time × supplementation interactions. We will also consider the order of both visits in a first intent and this factor will be kept in analyses only if significant. As all groups are matched by age, sex, and BMI, only medication intake, level of physical activity, glycemic excursions, risk for hypo- or hyperglycemia, and glycemic variability will be considered as covariates when analyzing data. In case of drop-outs or missing data, the participant is still included in data analysis providing one out of two visits is completed.

Results will be presented as mean ± standard deviation with its corresponding 95% confidence interval. Level of significance will be set at *p* < 0.05. Data analysis will be conducted using IBM SPSS statistics version 26.

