## Abstract

**Introduction:** Patients with type 2 diabetes mellitus are at high risk to develop vascular complications resulting in high morbidity and mortality. Cocoa flavanols are promising nutraceuticals with possible beneficial vascular effects in humans. However, limited research is currently available on the vascular effects in a diabetic population with inconsistent results. Possible reasons for this inconsistency might be heterogeneity in the given intervention (dose per time and day, single dose vs. split-dose, placebo formula) and the studied population (blood pressure at baseline, duration of diabetes, use of vasoactive antihypertensive and antidiabetic drugs, sex). Therefore, we aimed to develop a randomized, double-blinded, placebo-controlled cross-over trial to investigate whether cocoa flavanols have an acute impact on blood pressure and vascular reactivity in patients with type 2 diabetes with and without arterial hypertension.

**Methods and Analysis:** We will include participants in four groups: (i) patients with type 2 diabetes without arterial hypertension, (ii) patients with type 2 diabetes with arterial hypertension and 1 antihypertensive drug, (iii) non-diabetic participants with essential hypertension and 1 antihypertensive drug, and (iv) healthy controls. All participants will complete the same protocol on both testing days, consuming high-flavanol cocoa extract (790 mg flavanols) or placebo. Macrovascular endothelial function (flow-mediated dilation) and blood pressure will be measured before and after capsule ingestion. Forearm muscle vasoreactivity (near-infrared spectroscopy) and brachial artery blood flow (echo-doppler) will be assessed in response to a dynamic handgrip exercise test after capsule ingestion. Data will be analyzed with a random intercept model in mixed models.

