## Methods and Analysis

### Study Setting and Organization

The trial is a single center study and will be executed at the Ghent University Hospital (Belgium). All participants will complete the same protocol on both test days, however consuming a different type of capsules in a randomized order: high-flavanol cocoa extract or placebo. The flavanols used in this trial were extracted from the cocoa bean. A wash-out period of minimal 3 days and maximal 2 weeks is provided. The first measurement was conducted on October 5th, 2018 and since the COVID-19 pandemic forced to cancel all measurements for about 6 months, the end date of the study was postponed and is estimated in June 2021.

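### For FMD and blood pressure, a random intercept alone has no visit-level variance term, so any day-to-day variance makes between-visit standard errors too small and time × supplementation standard errors too large

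*Protocol article*

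**What the plan says.** The Data-Analysis Plan section of the protocol article says "Data will be analyzed using a random intercept model in mixed models", and the Abstract repeats it: "Data will be analyzed with a random intercept model in mixed models". No other random effect or residual covariance is named.

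The fixed effects are group, supplementation and "the time (pre- vs. post-intake of capsules) during each visit for repeated measurements", "as well as group × supplementation interaction and time × supplementation interactions". The visit appears once more, as a fixed effect: "We will also consider the order of both visits in a first intent and this factor will be kept in analyses only if significant".

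On the data structure, the Abstract states "Macrovascular endothelial function (flow-mediated dilation) and blood pressure will be measured before and after capsule ingestion". The handgrip outcomes (near-infrared spectroscopy and brachial blood flow) differ: they "will be assessed in response to a dynamic handgrip exercise test after capsule ingestion". On the spacing of visits, Study Setting and Organization says "A wash-out period of minimal 3 days and maximal 2 weeks is provided".

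**The concern.** FMD and blood pressure give four values per person, nested in two visits (for blood pressure, if the 3-minute readings are averaged per session). Two values from the same morning share whatever is particular to that day. Values from visits 3 to 14 days apart do not. A participant intercept cannot express this, because it gives every pair of values the same correlation.

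The listed terms draw on different levels of variation. Supplementation and group × supplementation compare one visit with the other, so visit variance belongs in their error. Time × supplementation compares changes within visits, so visit variance cancels. One pooled residual serves both badly, in opposite directions.

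Group × supplementation is the only listed test of whether the cocoa effect differs between the diabetic, hypertensive and healthy groups, and it would give too many false positives. Time × supplementation carries the acute effect, and it would lose power in a trial with groups of 10 to 30.

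**Working it through.** **Inputs from the protocol article.** Four values per person for FMD and blood pressure (Abstract). Planned groups of 15, 10, 30 and 20, total 75 (Eligibility Criteria). Significance level 0.05 (Data-Analysis Plan); two-sided is assumed, as sidedness is not stated.

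**Input not in the document.** The ratio r = σv²/σe², where σv² is the variance of visits within a person and σe² the residual variance. The values 0, 0.1, 0.25, 0.5 and 1.0 are assumptions. The plan states no figure for this point that could be reproduced. Its minimum of nine per group comes with no standard deviation and does not enter here.

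**Error variances, complete data.** Each person supplies three within-person contrasts:
- one between visits, with error variance σe² + 2σv²;
- two within visits, each with error variance σe².

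A model with only a participant intercept pools them: (σe² + 2σv² + σe² + σe²)/3 = σe² + (2/3)σv².

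**Standard error factors (stated model over correct).**
- Between-visit terms: √[(1 + 2r/3)/(1 + 2r)]
- Time × supplementation: √(1 + 2r/3)
- Single-contrast type I error: 2[1 − Φ(1.96 × factor)]
- Power for time × supplementation, where the correct standard error would give 80%: Φ(1.960 + 0.842 − 1.960 × factor)

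**Example, r = 0.5.** The pooled residual is 1 + 0.333 = 1.333.
- Between visits: √(1.333/2) = 0.816; 1.96 × 0.816 = 1.600; type I error 11.0%.
- Time × supplementation: √1.333 = 1.155; 1.96 × 1.155 = 2.263; type I error 2.4%.

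| r (assumed) | SE factor, between-visit | Type I error, one contrast | SE factor, time × supplementation | Type I error | Power (80% if correct) |
|---|---|---|---|---|---|
| 0 | 1.00 | 5.0% | 1.00 | 5.0% | 80% |
| 0.1 | 0.94 | 6.5% | 1.03 | 4.3% | 78.2% |
| 0.25 | 0.88 | 8.4% | 1.08 | 3.4% | 75.3% |
| 0.5 | 0.82 | 11.0% | 1.15 | 2.4% | 70.5% |
| 1.0 | 0.75 | 14.4% | 1.29 | 1.1% | 60.7% |

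**Simulation check.** 75 persons in the planned groups, complete data, 4,000 runs per setting, nominal 5%:

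| r | Supplementation | Group × supplementation (3 df) | Time × supplementation |
|---|---|---|---|
| 0 | 4.4% | 5.0% | 5.0% |
| 0.5 | 10.3% | 16.3% | 2.6% |
| 1.0 | 14.5% | 23.1% | 1.3% |

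The four-group test has 3 degrees of freedom and is inflated more than a single contrast.

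**Mixed-model check.** Both models were fitted to 60 simulated data sets at r = 1. Adding visit within participant moved the mean standard error for supplementation from 0.148 to 0.197 (0.148/0.197 = 0.75), and for time × supplementation from 0.296 to 0.230 (0.296/0.230 = 1.29), in units of σe. Both ratios match the closed form.

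**Does anything else stated absorb visit variance?** No. Order shifts the mean only, and is dropped if not significant. The activity and glycaemic covariates come from one week after the second study day (Additional Outcome Measures), so they describe the person and not the visit.

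**The case against.** The strongest reply is that a journal article condenses the plan. The repeated-measures wording could point to a residual covariance set out in a fuller document, since SPSS specifies that separately from random effects. This lowers confidence but does not answer the point. The phrase describes the time factor in a list of fixed effects, while the random intercept is stated twice as the model.

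A second reply is that the protocol works hard to make the two days alike. Guidelines for Participants sets the same evening meal, the timing of antihypertensives and limits on diet and exercise, and Study Protocol fixes the breakfast formula. This stands in part. These steps should reduce visit variance, which is why small ratios belong in the range. They do not remove it.

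Four stronger readings are tempting and are not supported:
- That the plan ignores the visit altogether. It considers order as a fixed effect; the gap is in the variance structure.
- That the tests have a known error rate of, say, 14%. The ratio is assumed, and at 0.1 the single-contrast figure is 6.5%.
- That every outcome is affected. Outcomes measured only after intake have two values per person, for which a participant intercept is enough.
- That adjusting for the pre-intake value would cut variance by a fixed 25–40%. That range assumes the covariate slope equals the within-person correlation. With raw pre-intake values beside a participant intercept, simulated reductions were about 14–19% or 23–29%, depending on the assumed between-person variance. The unadjusted contrast is also valid, so this is a matter of precision only.

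**Conclusion.** The point holds for FMD and blood pressure, conditionally on there being some day-to-day variance. The direction follows from the stated model: between-visit terms are anti-conservative and time × supplementation is conservative. The size cannot be fixed from the document; the tabulated figures rest on the assumed ratio, complete data and two-sided 5% tests. If visit variance is zero, the stated model is adequate. A reader should not infer that a positive time × supplementation result would be unsafe, because the error there costs power and does not create false positives. The amendment should be made before the data are analysed, and confidence in the practical size is medium.

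**What to change.** For outcomes measured before and after intake, state in the analysis plan that the SPSS mixed model has a random effect for visit within participant in addition to the participant intercept. Alternatively, replace the random intercept by an unstructured 4 × 4 covariance over visit × time. Keep the random intercept as it is for outcomes measured only after intake.

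The cost is a line of model specification and one extra variance component, with no new data. That component may be estimated at zero, in which case the results are essentially those of the stated model. The unstructured alternative estimates ten parameters (four variances and six covariances), which is heavier for 75 people.

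Optionally, constrain the pre-intake means to be equal under cocoa flavanols and placebo within that model. This can gain precision, but it changes the fixed effects and should be written down as a separate decision, with no promised size of gain.

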### Intervention

#### Study Protocol

As depicted in Figure 1, patients will arrive at the lab (Ghent University Hospital) at 8 o'clock after an overnight fast of minimal 8 h. Blood samples will be collected and participants will be evaluated for body composition [weight, height, skinfolds, and fat% (bio-electrical impedance analyzer)] and BP, followed by a standardized breakfast with negligible flavonoid and nitrate/nitrite amounts, in accordance to guidelines of a dietician (Table 3), and consumed within 15 min. Participants have to choose 1 formula of breakfast which will be consumed at both visits. After 15 min rest period, a baseline Flow-Mediated Dilation (FMD) measurement will be performed, followed by the ingestion of CF-enriched capsules (2.5 g of cocoa extract which contains 790 mg flavanols of which 150 mg epicatechin, *Naturex*^©^, *France*) or placebo (maltodextrin and an equivalent dose of theobromine and caffeine compared to the CF-enriched capsules) (Table 4). The dose of CF given in this study is based on the research of Balzer et al. (41) who investigated the effect of different doses of CF (high dose = 963 mg CF of which 203 mg epicatechin, medium dose = 371 mg CF of which 78.9 mg epicatechin, and low dose (control) = 75 mg CF of which 16.8 mg epicatechin), closely matched for theobromine and caffeine, on FMD in 10 patients with T2DM. The equilibration of theobromine and caffeine, both vasoactive compounds of cocoa (38, 56, 57), in the different interventions is a very important quality of this study and will ensure to test isolated vascular effects of CF.

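### For FMD and BP, the listed model isolates the cocoa flavanol effect only as a difference in change, which is less precise than adjusting for the pre-intake value already measured at each visit

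*Protocol article*

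**What the plan says.** The Data-Analysis Plan states: "Data will be analyzed using a random intercept model in mixed models". The fixed effects are group, supplementation and "the time (pre- vs. post-intake of capsules) during each visit for repeated measurements", "as well as group × supplementation interaction and time × supplementation interactions". Visit order is tried and kept only if significant. The covariate list is closed: "only medication intake, level of physical activity, glycemic excursions, risk for hypo- or hyperglycemia, and glycemic variability will be considered as covariates". Pre-intake FMD and BP are not on it.

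Under Study Protocol, "a baseline Flow-Mediated Dilation (FMD) measurement will be performed" after breakfast and before the capsules are swallowed. Under Blood Pressure, readings run "for 21 min with an interval of 3 min, pre- and post-capsules intake". The Abstract agrees: "Macrovascular endothelial function (flow-mediated dilation) and blood pressure will be measured before and after capsule ingestion". The forearm NIRS and brachial blood flow outcomes differ; they "will be assessed in response to a dynamic handgrip exercise test after capsule ingestion" and have no pre-intake value.

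**The concern.** Because time is a fixed effect, each participant contributes four FMD (or BP) values as outcomes: before and after intake, on CF and on placebo. Because supplementation is a main effect, the pre-intake means of the two conditions are estimated separately. Yet capsule order is randomised and the baseline precedes intake, so those means can differ only by chance.

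The supplementation and group × supplementation terms do not separate pre-intake from post-intake values. That leaves time × supplementation, which subtracts the chance baseline difference at full weight and adds its noise to the CF estimate.

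What is at stake is precision on FMD, the primary outcome, and on BP, from measurements the trial already takes.

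**Working it through.** **Inputs.** The model terms and covariate list come from the Data-Analysis Plan. Group sizes come from Eligibility Criteria: 15 + 10 + 30 + 20 = 75. I read the random intercept as one per participant. The document gives no SD and no within-visit or between-visit correlation, so ρ is assumed throughout.

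**The plan's own figure.** It states no variance ratio. Its minimum of nine per group cannot be reproduced, because no effect size or SD accompanies it. At n = 9, 80% power and two-sided 0.05, a paired t test needs a standardised difference of 1.07, but the SD in question is not given.

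**Step 1: the contrast.** Let D_pre and D_post be a participant's CF-minus-placebo differences before and after intake. With complete data, time × supplementation estimates the mean of D_post − D_pre.

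**Step 2: the variances.** Let both differences have variance V and correlation ρ = (within-visit − between-visit correlation)/(1 − between-visit correlation). Then:

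- Difference in change: 2V(1−ρ)/n
- Baseline-adjusted: V(1−ρ²)/n
- Ratio: 2(1−ρ)/[(1−ρ)(1+ρ)] = 2/(1+ρ)

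A random intercept alone makes all four values equally correlated, so ρ = 0 and the ratio is 2. The last column is used in Step 4.

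| ρ | Variance ratio 2/(1+ρ) | SE ratio | Planned / constrained, random intercept only: 2(1−ρ) |
|---|---|---|---|
| 0 | 2.00 | 1.41 | 2.0 |
| 0.3 | 1.54 | 1.24 | 1.4 |
| 0.5 | 1.33 | 1.15 | 1.0 |
| 0.7 | 1.18 | 1.08 | 0.6 |
| 0.8 | 1.11 | 1.05 | 0.4 |

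Exact generalised least squares agrees. With every correlation 0.50, the planned variance is 2.00 and the adjusted 1.00 (ratio 2.00). With within-visit 0.75 and between-visit 0.50, ρ = 0.25/0.50 = 0.5, and the variances are 1.00 and 0.75 (ratio 1.33).

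**Step 3: estimating the slope.** The formula treats the baseline slope as known. Simulation with the slope estimated gave:

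- Over 75 participants: 1.95, 1.58 and 1.32 at ρ = 0, 0.25 and 0.5.
- Within one group of 10: 1.73, 1.40 and 1.16.

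A common slope across groups therefore keeps most of the gain. Entering the raw baseline without the participant's mean baseline recovers less: about 1.64 at ρ = 0 and 1.2 at ρ = 0.5 (75 participants, 200 runs).

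**Step 4: constraining the pre-intake means.** If the pre-intake means are set equal but the random intercept stays the only covariance term, the model sees no covariance between D_pre and D_post. It gives D_pre zero weight and reduces to the raw post-intake difference, with variance V/n. The ratio is then 2(1−ρ), as in the last column: no gain at ρ = 0.5, and worse than the plan above it.

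**Step 5: unequal variances.** With variances V0 and V1 and covariance C, the difference in change has variance V0 + V1 − 2C and the adjusted estimate V1 − C²/V0. The gap is (V0 − C)²/V0, which is never negative. Unequal variances change the size of the gain but not its direction.

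**The case against.** **It is a matter of preference.** A difference in change is a standard, valid estimator, and covariance details often belong in an analysis plan that is not shown here. Part of this stands: nothing is contradicted or miscalculated. But the article is not silent. It lists the terms, leaves supplementation free at baseline, specifies only a random intercept and closes the covariate list.

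**It is biased.** A reader might infer this. It is not: randomised order keeps the difference in change unbiased.

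**The inflation is at least about 1.3.** The documents do not support a floor. They report no ρ, and the ratio falls below 1.3 once ρ exceeds about 0.54. The factor 2 is a limiting case, in which values from one morning are no more alike than values from visits at least 3 days apart. ρ may also differ by outcome, since baseline BP is taken before breakfast and baseline FMD after it.

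**Power falls from 80% to between 51% and 68%.** Those figures hold at ρ from 0 to 0.5 for a contrast within one group of 9 to 20. The listed terms contain no group × time × supplementation interaction, so the contrast at issue pools all 75 participants. As an illustration, assume an SD of 3.0 percentage points for the post-intake difference, an effect of 1.5 points and a paired t test at n = 75. Power is then 0.86 against 0.99 at ρ = 0, and 0.99 against 1.00 at ρ = 0.5.

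**The plan does not name the contrast.** True. That time × supplementation carries the CF effect is inferred from its being the only listed term that can.

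**The remedy has loose ends.** This stands for the covariate version. The plan keeps participants with one completed visit, whose deviation from their own mean baseline is zero by construction. It also discards badly tracked FMD data, so some baselines may be missing.

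**Conclusion.** The point holds as a loss of precision for FMD and BP. The only listed term that isolates a CF effect subtracts a pre-intake difference that randomisation makes pure chance. Given equal pre- and post-intake variances, this is less precise than baseline adjustment at any ρ below 1. The variance ratio is 2.0 under the plan's own random-intercept assumption. Otherwise it depends on an unreported ρ: 1.54 at 0.3, down to 1.11 at 0.8, and smaller if the slope is estimated within a single group of 10. NIRS and exercise blood flow are post-intake only and are unaffected. The change is worth making because it uses data already collected, not because the planned estimate is invalid.

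**What to change.** For FMD and BP, choose one of the following and write it into the analysis plan before unblinding.

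1. **Covariate version.** Model the post-intake value at each visit with group, supplementation, group × supplementation, visit order and a random participant intercept. Enter the pre-intake value as two covariates, the participant's mean baseline and the visit's deviation from it, each with one common slope across groups. State how a missing baseline and a participant with only one visit are handled.
2. **Constrained version.** Keep all four values as outcomes. Retain group, time and group × time, and let supplementation enter only through its post-intake terms, so that pre-intake means are equal for CF and placebo. Add a participant-by-visit random effect to the random intercept, or use an unstructured covariance; without this the option should not be used. This version also keeps visits with a missing baseline.

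The cost is analysis wording and one or two degrees of freedom, plus the missing-baseline rule in the first version.
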